#### 2.5.10. CPET and EVV.

Incremental CPET followed the routine of our laboratory and has been previously published.^[55,56]^ First, after strict recommendations for abstinence from stimulants and depressants and using only habitual medication, the individuals will be stimulated to pedal to 60 cycles minute^-1^ after 2-minutes of rest and 2-minutes of warm-up toward maximum work rate tolerance, meaning that they cannot pedal for more than 10 seconds over 50 cycles minute^-1^ under the stimulus of the examiner, and present subjective signs of intense exhaustion. The initial power of “0” W during the warm-up was increased by 16 W/minute^-1^. Breath-by-breath oxygen consumption (*V*´O_2_), exhaled carbon dioxide (*V*´CO_2_), minute ventilation (*V*´_E_), respiratory rate (*f*R), and tidal volume (*V*_T_) components were measured using a QUARK CPET metabolic chart (COSMED, Italy, 2016), calibrated at 2 moments with high precision gases (GAMA-GASES, São Paulo, Brazil) before each test. Heart rate (HR) and rhythm will be monitored using an ECG system (COSMED® Tx12 ECG, Italy, 2016), integrated into the metabolic system, and programmed to control an electromagnetically braked cycle ergometer, the Imbrasport CG-400 model (Imbramed^®^, Porto Alegre, Brazil, 2017). Continuous peripheral digital oximetry monitoring (COSMED, Italy, 2018) was also performed. During CPET, BP is measured using the auscultatory technique based on the Korotkoff method. Measurements will be performed at baseline, at 2-minute intervals, and at the exercise peak. EVV will be measured as described for RVV, taking into account the exercise values for *V*´_E_, *V*_T_, *f*R, and *P*_ET_CO2 (Protocol 4, Fig. 3). As variability metrics depend on the number of respiratory cycles during the variable exercise period, we divided SD1 and SD2 by the number of breath-by-breath measured data collected for each subject (SD1/n and SD2/n) as recommended.^[51,57]^

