#### 2.5.6. RVV.

During the 2^nd^ visit, the subjects will be admitted to a climatized lab room at ~7:00 hours after a light breakfast without stimulant foods and will be instructed to remain calm during the study protocol. They will be monitored using a QUARK metabolic system (QUARK CPET, COSMED, Rome, Italy, 2016) for breath-by-breath oxygen consumption (*V*´O_2_), minute ventilation (*V*´_E_), tidal volume (*V*_T_), breathing frequency (*f*R), end-tidal carbon dioxide (*P*_ET_CO2), and inspiratory/expiratory time (s) using a low-resistance calibrated turbine (COSMED, Rome, Italy, 2016). The analyzer was calibrated with 2-point precision gases (GAMA GASES, São Paulo, Brasil). The turbine was attached to a non-rebreathing 2-way valve connected to a naso-oral mask attached to the head with head straps (Hans-Rudolph Inc., USA, 2036 series, 2019). All trials will be registered in real time and saved for posterior analysis in accordance with previously published methods.^[50]^ Resting variability was measured using our previously described method.^[51]^ First, a non-linear evaluation of breath-by-breath signals using an *in house* Poincaré analysis algorithm will be performed using the “R^®^” free software program (http://www.R-project.org/) to calculate SD1 and SD2 for minute ventilation, tidal volume, and breathing frequency. The resting trial was performed in a seated position for 5 min (Protocol 1, Fig. 3).

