#### 2.6.2. Secondary outcomes.

The secondary outcomes were(i)changes in RVV and.(ii)changes in EVV, both after 8 weeks of meditation, c006Fmpared to control subjects. Any SD1 difference > 1.2 L (Figure S1, Supplemental Digital Content, http://links.lww.com/MD/I272), after 8 weeks of meditation will be considered a clinically significant result.

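### Exercise SD2 is computed on an incremental ramp with no stated trend removal, so for minute ventilation it mainly reflects the ventilatory rise and hardly registers breathing variability

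*Protocol article*

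**What the plan says.** Section 2.5.6 sets the resting method: a breath-by-breath Poincaré analysis "to calculate SD1 and SD2 for minute ventilation, tidal volume, and breathing frequency". The recording is level: "The resting trial was performed in a seated position for 5 min".

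Section 2.5.10 carries the method over to exercise: "EVV will be measured as described for RVV, taking into account the exercise values" of minute ventilation (V'E), tidal volume (VT), breathing frequency (fR) and end-tidal CO2 (PETCO2). The work rate starts at 0 W, "was increased by 16 W/minute^-1", and the test runs "toward maximum work rate tolerance". One exercise-specific step is given: "we divided SD1 and SD2 by the number of breath-by-breath measured data collected for each subject (SD1/n and SD2/n) as recommended".

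Section 2.6.2 lists as a secondary outcome "changes in EVV, both after 8 weeks of meditation", compared with control. Its relevance threshold of 1.2 L is on SD1; none is given for SD2. Section 2.10 analyses exercise ventilatory variability (EVV) by a mixed design with repeated measures, week 0 against week 8. It names no adjustment for the ventilatory rise. No section describes trend removal, a steady-state window or a common work-rate window.

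**The concern.** At rest the signal has no imposed trend, so SD2 describes slow fluctuation in breathing. On a ramp to tolerance, ventilation climbs several-fold, and that climb is itself spread along the line of identity. It enters SD2 in full and SD1 hardly at all, because SD1 is built from successive differences.

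Two things are at stake in the SD2 part of EVV. A true change in breathing variability could leave exercise SD2 of V'E almost unmoved. And a change in how steeply ventilation rises over the ramp could be reported as a change in variability.

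**Working it through.** The plan gives no figure for exercise SD2, so there is nothing to reproduce first.

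**Inputs from the protocol article.** Resting Poincaré method (2.5.6); ramp of 16 W/min from 0 W to maximum tolerance, with division by breath count n (2.5.10).

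**Assumed inputs (not in the documents).** V'E rise R of 30 to 75 L/min; breath-noise SD s of 1.5 to 5 L/min; lag-1 correlation phi of 0 to 0.6; duration 8 to 12 min.

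**Formulas.** SD1 = SD[(x(i+1) − x(i))/√2] and SD2 = SD[(x(i+1) + x(i))/√2]. A linear rise R has variance R²/12, which SD2² doubles. With stationary noise this gives:
- SD1² ≈ s²(1 − phi), with no term in R.
- SD2² ≈ R²/6 + s²(1 + phi).

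**Base case, V'E 12 to 60 L/min, phi = 0.3.** R²/6 = 48²/6 = 384.
- s = 3.6: s²(1 + phi) = 12.96 × 1.3 = 16.8. SD2 = √400.8 = 20.0. Trend share = 384/400.8 = 96%.
- s = 2.1: s²(1 + phi) = 4.41 × 1.3 = 5.7. SD2 = √389.7 = 19.7.
- So 71% more noise (3.6/2.1 = 1.71) raises SD2 by about 1%, while SD1 rises by the full 71% (√3.09 = 1.76 to √9.07 = 3.01).

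A simulation with a convex rise (9 min, 213 breaths) agrees: raw SD2 goes from 20.9 to 21.1. After a cubic trend is removed, SD2 goes from 2.33 to 3.99, up 71%.

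**Range for V'E.** For R of 30 to 60, s of 1.5 to 5 and phi of 0 to 0.6, the trend share of SD2² runs from 79% to 99.6%. At phi = 0.3, a 30% fall in noise moves SD2 by −0.1% to −4.6%; a 10% larger rise moves it by +8% to +10%.

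**Effect of dividing by n.** Since R dominates, SD2/n ≈ R/(n√6), the rise per breath. I simulated one fixed curve, V'E = 12 + 2.5t + 0.22t² with fR = 18 + 1.6t (t in minutes) and phi = 0.3. Stopped at 10 min (260 breaths, R = 47):

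| Noise SD | SD1 | SD2 | 1000 × SD2/n |
|---|---|---|---|
| 1.5 | 1.26 | 19.45 | 74.82 |
| 3.0 | 2.51 | 19.63 | 75.50 |
| 4.5 | 3.78 | 20.03 | 77.03 |

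Tripling the noise triples SD1 and moves SD2/n by 3% (77.03/74.82 = 1.03).

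With noise fixed at 1.5 and the same curve stopped at 8 and then 12 min, raw SD2 goes from 14.1 to 25.5. SD2/n (× 1000) goes only from 72.4 to 77.1, because n grows from 195 to 331.

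**Other signals (assumed ranges, treated as linear, phi = 0.3).**

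| Signal | Rise | Noise SD | Trend share of SD2² | SD2 change if noise falls 30% |
|---|---|---|---|---|
| VT | 1.0 L | 0.1 to 0.3 | 93% to 59% | −1.9% to −11.1% |
| fR | 17/min | 2 to 4 | 90% to 70% | −2.5% to −8.0% |
| PETCO2 | 5 mm Hg | 1 to 2 | 76% to 45% | −6.3% to −15.3% |

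**With detrending (V'E, convex ramp, cubic trend removed, phi = 0.3).** Noise SD 1.5 and 3.0 give SD2 of 1.68 and 3.34, whether the rise is 30 or 60 L/min. Without detrending the values are 12.9 and 13.2 (rise 30) and 25.6 and 25.7 (rise 60).

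**The case against.** The strongest case on the other side has four parts.

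- **Effort.** A reader might infer that exercise SD2 is a disguised measure of peak effort, so that motivation or a learning effect at the second test would pass for variability. That describes raw SD2, but the article analyses SD2/n. At a fixed ramp rate a subject who tries harder rides longer and takes more breaths. In a simulation with breathing rate assumed to go from 16 to 32/min, continuing along the same curve to 66 instead of 60 L/min raised raw SD2 by 12% (20.8 to 23.3). It raised SD2/n (× 1000) by about 1% (96.3 to 97.2). The effort reading is not supported; the insensitivity to variability stands.
- **SD1.** EVV includes SD1, the direct breath-to-breath measure, and the only relevance threshold is on SD1. The trend does not disturb unscaled SD1, so it would be wrong to say that a real change must go unseen. Nor does section 2.10 say that SD2 enters the correlation with carotid body activity; it names only the change in EVV. Both limits stand.
- **Other signals.** Near-blindness is shown for V'E only. This stands: the other three signals are diluted.
- **Silence.** The article relies on an in-house algorithm and cited method papers, and its data-collection figure is not shown. Trend removal may be in those sources. This stands as a caveat, but section 2.5.10 does say how the method is adapted for exercise, and it names only division by n.

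**Conclusion.** The point holds for the SD2 part of EVV. As written, exercise SD2 and SD2/n for V'E mainly measure the ventilatory rise, which for SD2/n is the rise per breath. In the base case 71% more breath noise moves SD2 by about 1%; on the fixed curve, tripling the noise moves SD2/n by 3%.

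The sizes rest on assumed ventilatory rises, noise levels and correlations. The V'E conclusion holds across the whole range tried, where the trend makes up at least 79% of SD2². It also rests on reading section 2.5.10 as a full account of the exercise adaptation.

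The consequence is mainly lost sensitivity, plus the risk that a changed ventilatory slope is called variability. It concerns one of two metrics of a secondary outcome in an exploratory trial and does not touch the primary outcomes. It is worth correcting before the exercise data are analysed.

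**What to change.** In section 2.5.10, state that each subject's trend against time or work rate is removed (for example by a cubic fit or a moving average) before exercise SD2 is computed, with the same rule at week 0 and week 8. If the in-house algorithm already does this, say so. State that SD1 carries the interpretation of breath-to-breath variability, and report undetrended SD2 as descriptive only.

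The cost is a sentence or two of text and a few lines in the R script. Section 2.5.6 says that the trials are saved for later analysis, so no new measurement is needed. The downside is that detrended SD2 is not directly comparable with the group's earlier values; reporting the undetrended figure alongside keeps that link.

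### Dividing exercise SD1 by breath count makes the EVV index depend on breath count; this biases the arm comparison only if breath count changes differently by arm

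*Protocol article*

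**What the plan says.** Section 2.5.6 defines the resting index: a Poincaré analysis is used "to calculate SD1 and SD2 for minute ventilation, tidal volume, and breathing frequency". The recording window is fixed ("The resting trial was performed in a seated position for 5 min"), and no division by breath count is described.

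Section 2.5.10 carries the method over to exercise: "EVV will be measured as described for RVV, taking into account the exercise values for" ventilation, tidal volume, breathing frequency and end-tidal CO2. It then adds a step. The stated reason is "As variability metrics depend on the number of respiratory cycles during the variable exercise period", and the step is "we divided SD1 and SD2 by the number of breath-by-breath measured data collected for each subject (SD1/n and SD2/n". Two references are cited in support.

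The exercise test has no fixed length. Work rate rises by 16 W per minute "toward maximum work rate tolerance".

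Section 2.6.2 makes EVV one of two secondary outcomes ("changes in EVV, both after 8 weeks of meditation", against control). Its significance threshold, "Any SD1 difference > 1.2 L", is not on a per-breath scale. Section 2.10 compares week 0 with week 8 in a mixed repeated-measures design. Neither 2.5.10 nor 2.10 states a matched exercise window.

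**The concern.** Dividing by n corrects for breath count only if the quantity divided grows in proportion to n. SD1 is a standard deviation of successive differences. For a given breath-to-breath variability its expected value is the same for 150 breaths as for 400, so dividing it by n introduces a dependence on n.

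Breath count is breathing rate times exercise time. In a symptom-limited test both can change between visits, and participants know whether they meditated or waited. If the two arms change in breath count by different amounts, the EVV comparison would show a difference with no change in variability. The percentage change in EVV is also correlated with the change in carotid body activity (section 2.10), so the artefact would enter that analysis too.

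**Working it through.** **Inputs from the article:** index SD1/n; symptom-limited test; 30 per arm analysable and 36 per arm recruited (2.4.6); two-sided alpha 0.05. **Assumed, not in the article:** 250 breaths; ventilation rising linearly from 10 to 60 L/min; lag-1 autocorrelation 0.3; noise either constant or proportional to ventilation; SD of log change 0.20 for SD1 and 0.10 for n. The article gives no figure of its own to reproduce.

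**1. Dependence of SD1 on n.** SD1 = SD(x[i+1] − x[i])/√2. A linear ramp adds a constant to each difference and drops out. Simulated SD1 with constant noise (SD 3 L/min) on a ramp is 2.52 at n = 150 and 2.51 at n = 400, while SD1/n falls from 0.0168 to 0.0063.

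**2. Fewer breaths, same ventilation range and duration.** SD1 is unchanged, so SD1/n is multiplied by 1/0.90 = 1.11. Simulation gives +11% under both noise models.

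**3. Test 10% longer at the same slope (ventilation reaches 65 L/min).**
- Constant noise: SD1 is unchanged, so SD1/n is multiplied by 1/1.10 = 0.909, or −9%.
- Proportional noise: SD1 follows the root mean square of ventilation. The mean square is (10² + 10×60 + 60²)/3 = 1433 for the shorter test and (10² + 10×65 + 65²)/3 = 1658 for the longer. SD1 rises by √(1658/1433) = 1.076, about 7.5%. SD1/n is multiplied by 1.076/1.10 = 0.978, about −2%.

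**4. False-positive rate with no effect on variability.** Assume the whole arm difference d in n passes into SD1/n. The SD of the log change is s = √(0.20² + 0.10²) = 0.224. The noncentrality is ln(1 + d)/(s√(2/m)) with m per arm, referred to the noncentral t on 2m − 2 degrees of freedom.

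| d | noncentrality, m = 30 / 36 | P<0.05, m = 30 / 36 |
|---|---|---|
| 2% | 0.34 / 0.38 | 6% / 7% |
| 5% | 0.85 / 0.93 | 13% / 15% |
| 10% | 1.65 / 1.81 | 37% / 43% |

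At d = 10% and m = 36, varying the two SDs over 0.15–0.30 and 0.05–0.15 moves the rate between 22% and 71%.

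**5. Precision when n changes equally in both arms.** If SD1 and n change independently, division multiplies the variance of the change by (0.20² + 0.10²)/0.20² = 1.25. If n varies through duration with proportional noise, the elasticity of SD1 on n is about 0.78. Taking 0.20 as the scatter unrelated to n, the ratio is (0.04 + 0.22²×0.01)/(0.04 + 0.78²×0.01) = 0.88. Division then improves precision.

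**6. Matched window.** Cutting the longer test at the work rate where the shorter one ended leaves undivided SD1 within 0.2% of its value in the shorter test under both noise models.

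**The case against.** The strongest reply is that the stated premise can be true of SD1. If breath-to-breath noise grows with ventilation, a longer test reaches higher ventilation and whole-test SD1 rises by about 7.5%. Dividing by n then removes most of that, and undivided whole-test SD1 is the worse index for duration. The article does not say which noise model applies. This stands: a reader might infer that simply dropping the divisor is safe, and it is not. The sensitivity to breathing rate, about 11%, remains under both models.

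A reader might also infer that the index favours meditation, because the introduction says lifestyle interventions can reduce exercise variability. The documents do not support this. The study's own prediction for breathing variability has no direction. Longer exercise lowers SD1/n and slower breathing raises it, so the two routes may partly cancel. Slow breathing is described during meditation, not during maximal exercise. Laboratory staff are to be blinded to allocation, and the end of the test has a pedalling-cadence criterion, which limits effort bias.

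Nor is 37–43% the trial's expected error rate. It rests on an assumed 10% arm difference in breath count that nothing in the article supplies.

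Finally, the argument does not carry over to SD2 unqualified. On a fixed-slope ramp SD2 does grow with test length (16.6 at n = 200, 32.8 at n = 400) and division roughly offsets it, though not when n changes through breathing rate. The study calls itself exploratory, EVV is secondary, and the division cites two sources not available here. These points limit the weight of the finding but do not alter the algebra for SD1.

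**Conclusion.** The point holds for SD1. As specified, the exercise index mixes breathing variability with breath count. The size is about 11% for a 10% fall in breath count at fixed ventilation and duration, and between 2% and 9% for a 10% longer test, depending on the noise model. The inverse dependence on n at constant SD1 is algebra; the other figures rest on the assumed ramp, noise and scatter.

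Bias between arms requires a differential change in breath count. That is plausible in an unblinded comparison with a symptom-limited test, but it is not shown and its direction is not known. Without it, the effect is on precision alone and may go either way. This is worth correcting before analysis; it does not touch the primary outcomes.

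**What to change.** In section 2.5.10, define the EVV outcome as undivided SD1 computed over the same work-rate range in both of a participant's tests, up to the lower of the two peak work rates. Because the ramp is fixed at 16 W per minute, this is the same exercise time from the start of the ramp. Report breath count and exercise time by arm and visit. Keep SD1/n only as a supplementary index for comparison with earlier work.

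Do not instead adjust whole-test SD1 for breath count or mean ventilation: both are measured after randomisation and may be affected by treatment.

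The cost is one change to the existing R algorithm and one sentence, with no new data. The late breaths of the longer test are not used, and the main index will differ from the laboratory's earlier publications.

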#### 2.5.11. Transcedental meditation (TM).

Transcendental meditation follows previously explored methods.^[58,59]^ A certified trainer will teach the TM technique to the group in the standard 4-day course preceded by an introductory briefing. The subjects will be widely informed about the method, receiving a 1-hour group-based introductory briefing about the method in the 1st session, followed by a personal interview, personal instruction session, and group verification sessions on 3 consecutive days following personal instruction. To verify the correctness of TM practice, group-based TM sessions will be performed once a week, guided by a senior professional therapist in a 20-minutes session in an appropriate and comfortable room while sitting comfortably with their eyes closed. During the week, the subjects will be trained to perform 2 20-minutes unsupervised sessions at home each day. TM will be implemented in a more cognitive fashion, with passive mental focusing associated with slow breathing. Predefined weekly contact by phone will be performed to check for adherence and adverse effects.

### 2.6. Outcomes

For participants who dropped out of the study at any time after randomization, researchers will use contact details to encourage them to undergo the end-study outcome assessments (8-weeks). Thus, outcomes will be assessed before and after the intervention period, regardless of attending or completion status.

#### 2.6.1. Primary outcomes.

The primary outcomes were as follows:(i)BP changes under normoxia.(ii)BP changes under hyperoxia, and.(iii)changes in RCBA after 8 weeks of TM compared with control subjects. Any BP difference for normoxic or hyperoxic trials > ± 5.9 mm Hg, as determined by our reliability study, after 8 weeks will be considered a clinically significant result (Figure S2 and S3, Supplemental Digital Content, http://links.lww.com/MD/I272). To the best of our knowledge, there has been no reproducibility study of the RCBA in adults with hypertension.

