#### 2.4.6. Sample size.

Since there are no previous studies on CB activity after meditation, our a priori sample size calculation was based on a previously cited pilot study on RCBA ^[47]^. Considering an effect size of 0.25, a minimum of 30 subjects would be necessary to detect a significant change in chemoreception based on within-group analysis. In addition, the sample size was calculated based on a pilot study. The pilot study comprised 12 normotensive/prehypertensive healthy subjects and showed a standard deviation of the mean difference for SBP ± 4.2 mm Hg, during 2 different trial days (see Supplemental Digital Content, http://links.lww.com/MD/I272), with the oscillometric method and under the same experimental conditions (normoxic, see subsection 2.5.7). Based on a repeated measure ANOVA design with 1 between-group factor (Meditators vs Control) and 2 within-groups factors (Gas type and Time), with 4 averaged BP measures [pre-normoxic (T1), pre-hyperoxic (T2), post-normoxic (T3), post-hyperoxic (T4)] for each subject, upon resting condition, 30 subjects per group would be adequate in a 2-sided study to set an error type I = 0.05 and *β* = 0.80. Considering a 20% dropout and exclusion rate, a minimum total sample size of 36 per group was required. This sample size is concordant with several studies on the effects of meditation on hypertension.^[47]^

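### The cut-offs for clinical significance do not fit the plan's own measures: ±5.9 mm Hg against a test-retest SD of 4.2, and 1.2 L against an exercise metric on the SD1/n scale

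*Protocol article*

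**What the plan says.** **Blood pressure.** Section 2.6.1 lists BP change under normoxia and under hyperoxia among the primary outcomes, compared with control. It gives one cut-off for clinical significance: "Any BP difference for normoxic or hyperoxic trials > ± 5.9 mm Hg, as determined by our reliability study". It does not say whether SBP or DBP is meant, or whether the cut-off is for a person or a group mean. Section 2.4.6 reports that a pilot "showed a standard deviation of the mean difference for SBP ± 4.2 mm Hg, during 2 different trial days", by oscillometry under normoxia. On its sample: "The pilot study comprised 12 normotensive/prehypertensive healthy subjects".

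**Ventilatory variability.** Section 2.6.2 lists changes in RVV, then "changes in EVV, both after 8 weeks of meditation", and follows both with a single rule: "Any SD1 difference > 1.2 L". Section 2.5.6 analyses resting breaths "to calculate SD1 and SD2 for minute ventilation, tidal volume, and breathing frequency". Section 2.5.10 states "EVV will be measured as described for RVV, taking into account the exercise values for" minute ventilation, tidal volume, breathing frequency and end-tidal CO2. Because the exercise period varies in length, "we divided SD1 and SD2 by the number of breath-by-breath measured data collected for each subject (SD1/n and SD2/n").

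**The concern.** A cut-off that comes from a reliability study should match that study's SD, and it should be used only for the quantity it bounds. Here 5.9 lies below the usual 95% limit implied by 4.2. It is also called clinically significant, although a measurement-error bound shows only that a change in one person is hard to explain by noise.

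The 1.2 L rule is on a different scale from the exercise outcome that it follows, and it has the wrong unit for several of the signals.

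Separately, dividing SD1 by breath count is meant to remove dependence on the number of breaths. For SD1 it may add that dependence.

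What is at stake is which results the report calls clinically significant, and whether a change in exercise SD1/n reflects variability or only breath count.

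**Working it through.** **1. BP cut-off**

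Inputs: SD of between-day SBP differences 4.2 mm Hg, n = 12 (Section 2.4.6); cut-off 5.9 mm Hg (Section 2.6.1).

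Trying to reproduce 5.9 from 4.2:
- 95% test-retest limit, 1.96 × SD of differences: 1.96 × 4.2 = 8.23
- the same with t on 11 df: 9.24
- 90% limit: 1.645 × 4.2 = 6.91
- 4.2 read as a within-subject SD: 1.96 × √2 × 4.2 = 11.6
- √2 × 4.2 = 5.94, and 1.96 × 4.2/√2 = 5.82

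Only the last line comes near 5.9, and neither expression is the 95% limit for a difference between two days. For 5.9 to be that limit, the SD of differences would have to be 5.9/1.96 = 3.01.

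Uncertainty from n = 12: the 95% CI for the SD is 4.2 × √(11/χ²), with χ² taken at its 97.5% and 2.5% points on 11 df. This gives 2.98 to 7.13. The limit then runs from 1.96 × 2.98 = 5.8 to 1.96 × 7.13 = 14.0.

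If 5.9 were applied to individuals: 5.9/4.2 = 1.40, and 2 × (1 − Φ(1.40)) = 0.16. With no true change and no bias, about 16% of persons exceed it on each comparison, or 0.16 × 30 = 4.8 of 30. At the two ends of the CI for the SD, 5.9/2.98 = 1.98 gives about 5% and 5.9/7.13 = 0.83 gives about 41%.

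If 5.9 were applied to group means: the standard error of a between-arm difference in change, with 30 per arm and SD 4.2, is 4.2 × √(2/30) = 1.08 mm Hg. Noise in the comparison of means is on that scale. A limit for one person's two readings says nothing about whether a mean difference matters clinically.

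**2. The 1.2 L cut-off on the EVV scale**

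Inputs: 1.2 L (Section 2.6.2); EVV as SD1/n (Section 2.5.10). The breath count is not given, so 150 to 350 is assumed.
- Raw SD1 difference needed for a difference of 1.2 in SD1/n, with equal n at both visits: 1.2 × 150 = 180; 1.2 × 350 = 420.
- Conversely, a raw difference of 1.2 becomes 1.2/150 = 0.008 or 1.2/350 = 0.003 in SD1/n.

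Units: litres cannot apply to breathing frequency (rest and exercise) or to end-tidal CO2 (exercise). Minute ventilation is volume per minute, so the unit leaves the intended signal open even at rest.

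**3. Dividing by n**

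In a Poincaré analysis SD1 is the SD of successive breath-to-breath differences divided by √2. Under steady short-term variability it does not grow with n, so SD1/n changes as 1/n:
- 250 to 275 breaths: 250/275 − 1 = −9%
- 250 to 300 breaths: 250/300 − 1 = −17%

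SD2 differs, because it reflects the longer trend. For a linear trend of slope a per breath, the SD of the series is a × √((n² − 1)/12), roughly proportional to n. The exercise test is a fixed-increment ramp, so SD2 may grow with n, and the arithmetic above does not carry over to SD2/n.

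**The case against.** **5.9 may be right for its source.** The supplementary figures cited for it are not shown, and 4.2 is for normoxic SBP only. The article neither calls 5.9 a 95% limit nor says that it comes from 4.2. A reader might infer a plain arithmetic error; the documents do not support that. With n = 12, 5.9 also lies just inside the range for the limit. What remains is that Section 2.6.1 applies 5.9 to any BP difference, including normoxic SBP, for which 4.2 is the only SD given.

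**No individual classification is planned.** Section 2.10 has no responder analysis, so the 16% enters no described test. That stands. It leaves the group reading, for which a repeatability limit is not the yardstick.

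**The detectable difference.** A reader might infer that 5.9 dismisses effects the trial is sized to detect. Section 2.4.6 states no target BP difference. A simple two-group formula with SD 4.2 gives (1.96 + 0.84) × 1.08 = 3.0 mm Hg at 80% power, but this carries a healthy-subject, two-day SD over to 8-week change in hypertension. At an SD of change of 8.16 the same formula gives 5.9 and the gap is gone. A relevance threshold above the detectable difference is also not an error in itself.

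**1.2 L may be meant for rest only.** The symbol (SD1, not SD1/n) and the unit suggest this. It is plausible, but Section 2.6.2 sets the rule after both outcomes without restriction. It would go too far to say that the authors intended a rule for EVV that can never be met.

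**SD1/n follows cited recommendations.** The sources cannot be checked here. A reader might infer that dividing by n is wrong for both metrics; because of the trend in a ramp test, the objection holds for SD1/n only. Whether meditation changes exercise duration or breath count is not known from the documents.

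**Conclusion.** The concern holds in three limited parts.

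1. As written, ±5.9 mm Hg does not match the stated SD. The implied 95% limit for normoxic SBP is about 8.2 mm Hg (5.8 to 14.0 given n = 12). In either use, a measurement-error bound does not establish clinical importance for the between-group difference that the primary outcome concerns. The 8.2 assumes that the pilot SD describes the same kind of measurement, and it comes from normotensive or prehypertensive subjects, not the trial population.

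2. The 1.2 L cut-off cannot be used on the SD1/n scale or for signals not measured in litres. The 180 to 420 rests on the assumed breath counts.

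3. For SD1, division by n brings in the dependence on breath count that it is meant to remove: −17% from 250 to 300 breaths with SD1 unchanged.

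The cut-offs do not enter the ANOVA tests of Section 2.10, so the type I error of those tests is unaffected. The first two parts concern how results are labelled; the third concerns what the exercise SD1 metric measures. In a study described as exploratory this should be corrected, but it does not undermine the design.

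**What to change.** - **BP:** judge relevance on the between-arm difference and its 95% CI against a separately justified difference. State how 5.9 was derived and for which component and gas. Use a repeatability limit only to describe individual changes: 8.2 mm Hg for normoxic SBP from the stated SD, and its own value for each other BP component and gas.
- **SD1 cut-off:** restrict 1.2 L to the resting SD1 of the signal and unit it was derived for.
- **EVV:** alongside SD1/n, report undivided exercise SD1 from the recorded signals, over a comparable work-rate segment at weeks 0 and 8.

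Cost: the first two are changes of wording, plus the justification of a relevant BP difference. The third is a little extra analysis of signals already recorded. The undivided SD1 will be less directly comparable with earlier SD1/n reports, which is why SD1/n is kept beside it.
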